#### Data collection and management

An electronic data capture (EDC) system will be developed for data collection and management. Pre-validated case report forms (CRFs) will be used to collect demographic information, clinical outcomes, AEs, and adherence to the protocol. Data will be collected longitudinally at baseline, on the 10th and 20th days of treatment, and at 1 and 3 months after treatment. The data entry process will begin with built-in checks and logical validations in the EDC system to reduce errors. Trained personnel will conduct double-entry validation. Custom scripts in the R language will be used to automatically conduct logical checks for outliers and inconsistencies. A three-stage coordination process will be adopted: outliers or missing data will be automatically detected, 10% manual comparisons between CRFs and the database will be randomly conducted, and senior data managers will arbitrate unresolved issues. All data will be stored on a password-protected server, using role-based access control. Patient identifiers will be anonymized through a unique study code. The main list will be stored separately, and daily encrypted cloud backups will be made. The anonymous dataset will be archived for ≥5 years after publication. Access to the original data needs approval from the principal investigator and the ethics committee. The database will be locked after blind review by an independent group. Before locking, all data queries will be resolved, the final analysis population will be determined, and the statistical analysis plan will be consistent with the protocol. After signing the data lock certificate, read-only access will be activated.

#### Quality control

Before its implementation, the trial protocol will be subjected to independent expert review, including experts in acupuncture rehabilitation, orthopedics, biostatistics, clinical methodology, etc., to ensure its scientific validity. All researchers will receive mandatory training covering patient screening, standardized acupuncture techniques, and EDC operations to ensure consistent operations. Independent auditors will conduct regular on-site supervision, verifying the protocol’s implementation, randomly selecting 10% of the clinical report forms for review, and promptly reviewing AE records. The EDC platform will be employed to ensure data quality through detailed modification audit records, automatic logical checks for outliers, and role-based access control to prevent unauthorized editing. Additionally, a three-level data monitoring committee will be established to ensure data integrity and participant safety. The primary monitor will be responsible for real-time program supervision during the intervention period; the secondary monitor (ethics and compliance experts) will review informed consent documents, track AES following CTCAE v5.0 standards, and ensure timely reporting of serious AEs to the TSC. The tertiary monitor (biostatisticians and data managers) will verify the dataset through double-entry validation and automated logical checks, resolve discrepancies, and ensure compliance with the pre-defined statistical analysis plan.

#### Confidentiality and ethics compliance

Patient privacy will be preserved by anonymizing all records. Data sharing will comply with ethical standards, and de-identified datasets will be accessible upon reasonable requests after publication.

#### Statistical methods

All statistical analyses will be conducted by an independent statistician blinded to group allocation. A two-sided significance level of *α* = 0.05 will be applied for all inferential tests.

#### Analysis populations

The intention-to-treat (ITT) population will include all randomized participants.

The per-protocol (PP) population will comprise participants who complete at least one intervention session and provide primary outcome data at the end of treatment (day 20).

#### Handling of missing data

Missing data will be addressed using multiple imputation by chained equations (MICE), producing 20 imputed datasets. Sensitivity analyses will be conducted to compare the results from the imputed datasets with those from complete-case analyses to assess robustness.

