### Criteria for discontinuation of the intervention

Participant involvement in the trial may end early due to the following reasons:

Serious adverse event (SAE): Discontinue immediately if the investigator links an SAE to acupuncture or rTMS.

Withdrawal of consent: Participants may voluntarily withdraw consent at any time without a reason.

Protocol violation: Major deviations that compromise safety or data integrity, as judged by the principal investigator (e.g., starting prohibited treatments or finding ineligibility after randomization).

Loss to follow-up: Participant cannot be reached for three sessions or assessments.

Clinical deterioration: An independent clinician confirms a decline in health status, making participation unsafe or impractical.

Investigator’s decision: The investigator may stop intervention for any reason, protecting the participant’s best interest.

For all participants discontinuing the treatment, the reason and the date of withdrawal will be recorded in the case report form. We attempt to assess the final outcome at discontinuation.

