### Handling of missing data

For the primary ITT analysis, missing data will be handled using multiple imputation by chained equations (MICE). The details are described in the statistical plan.

Sensitivity analyses will be used to compare the results of the imputed ITT population with those of the complete-case PP population to assess the robustness of the results.

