#### Sample size

Sample size was calculated using G*Power 3.1.9.7 software (40), based on the primary outcome measure of pain intensity assessed by the VAS. Key parameters were set as follows: a minimum clinically important difference (MCID) of 1.5 points on the VAS, a standard deviation (SD) of 1.8 points derived from pilot data, a two-tailed significance level (*α*) of 0.05, and a statistical power (1 − *β*) of 90%. For the three-arm parallel design, which is meant to be analyzed using one-way analysis of variance (ANOVA), an effect size (f) of 0.42 (classified as Cohen’s medium-to-large effect) was estimated (25). The initial calculation indicated a requirement of 33 participants per group. To account for a conservative dropout rate of 20%, resulting in a final allocation of 42 participants per group (total *N* = 126).

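### Comparing multiple imputation with complete-case results cannot show robustness to dropout that depends on unobserved pain, because both estimates are then biased by nearly the same amount

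*Protocol article*

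**What the plan says.** Missing-data handling appears in two places in the protocol article.

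- Statistical methods, Handling of missing data: MICE with 20 imputed datasets, then "Sensitivity analyses will be conducted to compare the results from the imputed datasets with those from complete-case analyses to assess robustness".
- The section of the same name after Exclusion from PP analysis: MICE for the primary ITT analysis, details left to the statistical plan, and a sensitivity analysis to "compare the results of the imputed ITT population with those of the complete-case PP population to assess the robustness of the results".

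The other sensitivity analyses named are ITT against PP, non-parametric alternatives if model assumptions fail (Subgroup and sensitivity analyses), and exclusion of frequent rescue-medication users (Exploratory and safety analyses). None changes the assumption made about unobserved pain scores. Both descriptions of the PP set (Exclusion from PP analysis; Analysis populations) require a day-20 VAS, so the PP comparison is also an observed-case analysis.

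The Sample size section reads "To account for a conservative dropout rate of 20"%. Among the grounds for ending participation is "Clinical deterioration: An independent clinician confirms a decline in health status, making participation unsafe or impractical". The same section says that a final assessment will be attempted at discontinuation.

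**The concern.** A sensitivity analysis for missing data should show whether the conclusion survives a plausible change in what is assumed about the values nobody saw. Standard MICE draws those values as if dropouts resembled participants in the same arm with the same observed history. Complete case leaves the dropouts out. Neither result moves with how much pain the dropouts really had at the missed visit.

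If patients leave because pain is worsening in ways the recorded visits do not capture, both estimates are wrong together. The protocol foresees deterioration and treatment-linked serious adverse events as reasons for leaving, so some outcome-related loss is plausible. The stake is how agreement would be read: a reader would take it as reassurance about the primary pain contrasts, when for this kind of dropout it carries no information.

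The second version of the check, imputed ITT against complete-case PP, changes the population and the missing-data method at once, so a difference there could not be attributed to either.

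**Working it through.** **The plan's own figures.** From Sample size: 33 per group before dropout, "a standard deviation (SD) of 1.8 points derived from pilot data", "a minimum clinically important difference (MCID) of 1.5 points on the VAS", and 20% dropout. 33 / (1 − 0.20) = 41.25, rounded up to 42 per group; 3 × 42 = 126. This reproduces the plan and gives the inputs used below: 42 per arm, SD 1.8, 20% missing. The two-sided 5% level comes from Statistical methods.

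**Assumptions not in the documents.** Visit correlation 0.5 (range 0.3 to 0.7 where stated), dropout at the planned rate in each arm, and the size and direction of the MNAR shift. A day-20 ANCOVA on baseline stands in for the planned mixed model.

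**Bias by arithmetic.** Let a fraction p of an arm be missing, and let those patients have δ points more pain than missing at random (MAR) predicts. The true arm mean is (1 − p) × observed + p × (MAR prediction + δ). MICE under MAR omits p × δ. If dropout is otherwise unrelated to outcome given the covariates, complete case omits the same quantity. The error in the contrast, in favour of YLDJJ, is therefore

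spurious benefit = p(Y) × δ(Y) − p(C) × δ(C).

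- δ(Y) = 1.5, δ(C) = 0: 0.20 × 1.5 = 0.30 points.
- δ(Y) = 3, δ(C) = 0: 0.20 × 3 = 0.60 points.
- Equal δ and equal dropout in both arms: 0.
- Larger δ in the comparator: the error runs against YLDJJ.

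**Approximate false-positive rate.** Completers per arm: 0.80 × 42 = 33.6. SE = 1.8 × √(1 − 0.5²) × √(2 / 33.6) = 0.380. For 0.30: 0.30 / 0.380 = 0.79 SE, giving about 12% two-sided. For 0.60: 0.60 / 0.380 = 1.58 SE, giving about 35%.

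**Simulation with a fixed shift, true effect 0.** Two separately built simulations of the YLDJJ-versus-sham contrast:

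| | δ = 0 | δ = 1.5 | δ = 3 |
|---|---|---|---|
| Spurious benefit, about equal in both analyses | 0 | 0.28 to 0.33 | 0.58 to 0.59 |
| False positives (nominal 5%) | about 6% | 10 to 14% | 31 to 34% |
| Same significance conclusion | 98% | about 95 to 97% for both shifts | |

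Agreement is nearly the same with and without bias, so it does not separate the two situations.

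**Simulation with high-pain YLDJJ patients dropping out.** Here dropout depends on the missing pain score itself, and control dropout is random. At correlations 0.3 / 0.5 / 0.7, the bias under imputation is −0.44 / −0.39 / −0.25 and under complete case −0.45 / −0.41 / −0.28. When imputation was falsely significant, complete case was too in 90 to 92% of runs. At correlation 0.5 the mean absolute gap between the two estimates was 0.06 points, the same as under completely random dropout.

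**Where the comparison does work.** When dropout follows day-10 VAS, which is recorded, imputation stays unbiased (−0.02 to +0.01) while complete case is biased by −0.12 to −0.27. At correlation 0.5, with this dropout in the YLDJJ arm, the mean absolute gap rises to 0.15. With strong dependence and 30% dropout, complete-case bias reaches about −0.45 and the significance verdicts agree in only 80 to 83% of runs.

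**The case against.** A reader might infer that the two methods share one assumption, so that the check would call the result robust almost whatever happened. The documents and the calculation do not support that. Imputation needs MAR given everything in the imputation model, which can include interim VAS. Complete case needs missingness unrelated to outcome given the analysis covariates alone, usually a stronger condition. The two diverge when dropout follows observed interim pain, so the comparison has a real use.

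Nor does the protocol state that agreement counts as robustness. It says only that results will be compared for that purpose, with no threshold.

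It is also tempting to say that dropout will manufacture a YLDJJ benefit. Nothing in the documents fixes the direction. Deterioration could be as common under sham, and equal shifts cancel. The planned 20% is described as conservative, and the attempted assessment at discontinuation would recover some late pain values, although it does not replace a missed day-20 or follow-up visit.

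Finally, the statistical plan is not shown and may contain an MNAR analysis. That is why the point is confined to the check that the protocol itself fixes. The complaint about mixing ITT and PP is likewise softened, because the Statistical methods section separately plans a plain imputed-versus-complete-case comparison.

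What remains after all this: divergence can reveal one kind of dropout, but agreement cannot exclude the other.

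**Conclusion.** The point holds in this limited form. The robustness check named in both missing-data sections does not address dropout that depends on unobserved pain, and no other sensitivity analysis in the protocol does. Under the assumed one-sided scenario, both analyses show a spurious benefit of about 0.3 to 0.6 points, false-positive rates rise from 5% to roughly 10 to 34%, and the verdicts coincide in about 95 to 97% of trials.

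These sizes rest on the assumed shift, its direction, the correlation and a simplified model. They show what could go undetected and do not predict what will happen.

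The importance depends on the margin of the result. Holding the SE at 0.380, significance is lost when the contrast falls below 1.96 × 0.380 = 0.745. With 20% missing in the YLDJJ arm, an estimate of 1.5 points would need a shift of (1.5 − 0.745) / 0.20 = about 3.8 points. An estimate of 1.0 would need only (1.0 − 0.745) / 0.20 = about 1.3.

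**What to change.** In both missing-data sections, make the robustness check a delta-adjusted (tipping-point) analysis within the planned MICE. Add a range of shifts to the imputed VAS, for example 0 to 3 points in steps of 0.5, varied by arm: YLDJJ alone, and the comparators as well. For each pre-planned contrast, report the delta at which significance is lost, so that readers can judge its plausibility. With 20% missing, each point of delta moves the contrast by 0.20, which makes the result easy to interpret. An imputation of the active arms from the sham arm is a reasonable optional addition.

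Keep imputed versus complete case as a supplement, described as informative about dropout related to observed pain. Report ITT versus PP separately as an adherence analysis. If the statistical plan already contains an MNAR analysis, a reference to it in these two sections is enough.

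The cost is a few sentences and some extra runs in the mice package already named. Sample size and data collection do not change. The robustness statement may turn out less favourable.

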#### Descriptive statistics

Baseline characteristics will be summarized as follows:

Normally distributed continuous variables (e.g., age and baseline VAS score) will be expressed as mean ± standard deviation (M ± SD) and compared using one-way ANOVA to assess homogeneity across the three groups before intervention.

Non-normally distributed continuous variables will be reported as medians and compared using the Kruskal-Wallis test.

Categorical variables (e.g., sex and stroke type) will be presented as frequencies and compared using *χ*^2^ or Fisher’s exact test.

To control for its potential confounding effect, pre-stroke hand dominance will be recorded and included as a covariate (categorical variable: right-dominant, left-dominant) in the linear mixed-effects models for outcomes in which functional compensation is a key factor, such as the modified Barthel index (MBI), to control for its potential confounding effect.

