### Eligibility criteria

#### Inclusion criteria

(1) Confirmed diagnosis of CRPS-I based on the Budapest clinical diagnostic criteria.(2) CRPS-I secondary to ischemic or hemorrhagic stroke confirmed based on CT/MRI within 3–12 months before enrollment.(3) Mean pain intensity ≥4 on the visual analogue scale (VAS; 0–10 cm) during 7 days before the intervention.(4) Unilateral upper-limb pain localized to the hemiparetic extremity.(5) Neurologically stable status, defined as a National Institutes of Health stroke scale (NIHSS) score ≤15.(6) Adequate tolerability for both acupuncture and repetitive rTMS interventions.(7) Aged between 18 and 80 years at screening.(8) Documented hand dominance before stroke.(9) Provision of written informed consent voluntarily obtained before participating in the trial.

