#### Acupuncture technique

Sterilized disposable stainless steel needles (0.30 mm × 40 mm, Hwato) will be employed. The insertion depth will range from 10 to 25 mm based on anatomical location. A standardized reinforcing-reducing manipulation will be applied, involving uniform lifting, thrusting, and rotating maneuvers at 60–90 cycles per minute for 20–30 s per acupoint to achieve deqi.

Deqi definition: Deqi is defined as a combination of subjective sensations reported by the patient (e.g., soreness, numbness, heaviness, and distension) and the objective sensation of needle grasp felt by the practitioner (34, 35). Needle retention: Needles will remain *in situ* for 30 min.

Treatment schedule: Sessions will be conducted once daily, 5 days per week, for a total of 20 sessions over 4 weeks. Each session will last approximately 40 min.

For rTMS, stimulation will be delivered to the contralateral M1 hand area using the Shenzhen Yingzhi M-50 apparatus. The M1 hand area will be identified using the international 10–20 EEG system for scalp electrode placement, with the target site at C3 (for right hemiparesis) or C4 (for left hemiparesis). The resting motor threshold (RMT) will be determined before the first treatment session to individualize stimulation intensity. Key parameters, including frequency, intensity, and pulse configuration, are summarized in Table 2. The schematic diagram of M1 is shown in Figure 3.

**Table 2 tab2:** Parameters for repetitive rTMS protocol.

Parameter	Specification
Device	Shenzhen Yingzhi liquid-cooled circulating M-50 Ultimale rTMS therapeutic apparatus
Stimulation site	Contralateral primary motor cortex hand area corresponding to the painful limb(M1)
Frequency	10 Hz
Intensity	80–120% of resting motor threshold
Trains per session	20
Pulses per train	1 pulses per train
Train duration	10 s
Inter-train interval	10 s
Total pulses/session	2,000
Session duration	19 min 50 s
Treatment schedule	Once daily for 20 consecutive days

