#### Activities of daily living (ADL)

ADL will be assessed using the modified Barthel index (MBI), which covers domains such as feeding, dressing, toileting, continence, and mobility. Scores will range from 0 to 100, with higher scores indicating greater degrees of independence.

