#### Primary outcome analysis

Pain intensity, measured based on the VAS, will be analyzed using a linear mixed-effects model (LMM). Fixed effects will include group, time, group-by-time interaction, baseline VAS score, and rescue medication use. Random effects will account for participant-specific intercepts. Between-group differences at each time point will be estimated with 95% confidence intervals (CIs). A reduction of ≥1.5 points from baseline will be considered clinically meaningful. Pre-planned contrasts will be conducted to test the following hypotheses: (1) the experimental group (YLDJJ + rTMS) will be superior to control group 2 (sham acupuncture + rTMS); and (2) the experimental group will be superior to control group 1 (conventional acupuncture + rTMS). These comparisons will directly test the specific efficacy of YLDJJ acupuncture with those of both a sham control and a conventional acupuncture active control.

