#### Secondary outcomes analysis

Continuous outcomes (CRPS severity score, FMA, MBI, infrared thermography ΔT, and rs-fMRI connectivity) will be analyzed using the same LMM specification as the primary outcome.

Ordinal outcomes (Brunnstrom stages and MAS) will be analyzed using generalized estimating equations (GEE) with a cumulative logit link function.

Categorical outcomes (e.g., AE adverse event causality) will be compared using *χ*^2^ or Fisher’s exact test.

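### Hand dominance is coded right/left without the paretic side, so it carries little information on whether the dominant hand is the affected one; a small, free improvement to the Barthel index model

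*Protocol article*

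**What the plan says.** All references are to the protocol article.

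- **Covariate and purpose (Descriptive statistics).** Pre-stroke dominance is to be "included as a covariate (categorical variable: right-dominant, left-dominant) in the linear mixed-effects models for outcomes in which functional compensation is a key factor". The MBI is the one outcome named as an example, and the aim given is to deal with possible confounding by dominance. The two levels are written out, so the coding is a stated choice and not a detail left to a later document.
- **Eligibility (Inclusion criteria).** Entry requires "Documented hand dominance before stroke" and "Unilateral upper-limb pain localized to the hemiparetic extremity". Neither criterion restricts the side.
- **Both sides enrolled (Acupuncture technique, experimental group).** The coil is placed "with the target site at C3 (for right hemiparesis) or C4 (for left hemiparesis").
- **Base model (Primary outcome analysis).** "Fixed effects will include group, time, group-by-time interaction, baseline VAS score, and rescue medication use".
- **Model for the MBI (Secondary outcomes analysis).** The continuous secondary outcomes, MBI among them, "will be analyzed using the same LMM specification as the primary outcome". That specification contains no dominance term, no paretic side and no product of the two.
- **Elsewhere.** Allocation of interventions states no stratification by side or dominance, and the planned subgroups use stroke type and NIHSS only.

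**The concern.** The article gives functional compensation as the reason for the covariate. For hand-dependent tasks, the contrast that plausibly matters is whether the paretic hand is the one the patient relied on before the stroke. That depends on dominance and paretic side together. The plan records the first and leaves the second out of the model, so the two opposite cases among right-handers share one value.

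What is at stake is modest. The MBI model would carry a term that hardly varies between participants and would not adjust for the factor that motivates it. A report saying that the MBI was adjusted for dominance-related compensation would claim more than the model delivers.

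**Working it through.** The plan gives no figure on this point, so there is none to reproduce. The check asks how much the planned covariate tells us about the variable of interest.

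**Inputs from the article:** 126 participants, 42 per arm (Sample size); two-level dominance (Descriptive statistics); either side paretic (Inclusion criteria; Acupuncture technique).

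**Assumptions, since the article gives neither frequency:** proportion right-dominant p = 0.85 to 0.95; proportion with right paresis q = 0.4 to 0.7; the two independent.

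**Step 1. Formula.** Let C = 1 if the dominant side is the paretic side.

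P(C) = pq + (1 − p)(1 − q)

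The squared correlation between right/left dominance and C is

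R² = (2q − 1)² p(1 − p) / [P(C)(1 − P(C))].

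**Step 2. Results for dominance alone.**

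| p | q = 0.5 | q = 0.4 or 0.6 | q = 0.7 |
|---|---|---|---|
| 0.85 | 0 | 2.1% | 8.9% |
| 0.90 | 0 | 1.5% | 6.4% |
| 0.95 | 0 | 0.8% | 3.5% |

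Worked example for the largest value (p = 0.85, q = 0.7): P(C) = 0.595 + 0.045 = 0.64, and R² = 0.16 × 0.1275 / (0.64 × 0.36) = 0.0204 / 0.2304 = 0.0885. Replacing q by 1 − q leaves R² unchanged, so q = 0.3 gives the same values as q = 0.7.

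Over the same grid, paretic side alone would explain about 45% to 81% of the variance in C. The derived yes/no variable explains all of it by construction. The missing piece is therefore the side.

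**Step 3. How thin the planned covariate is.** Left-dominant participants expected: 126 × 0.05 = 6.3 to 126 × 0.15 = 18.9 in total, or 42 × 0.05 = 2.1 to 42 × 0.15 = 6.3 per arm. With q = 0.5, C splits the sample 126 × 0.5 = 63 to 63.

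**Step 4. Effect on the MBI comparison.** Assume C is split evenly and shifts baseline-adjusted MBI by d = 0.3 to 0.5 SD. The article gives no such value. Take a single time point with 42 per arm.

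- Variance explained by C: 0.25 × d² = 0.25 × 0.09 = 2.3% to 0.25 × 0.25 = 6.3%.
- Standard error inflation from leaving C out: 1/√(1 − 0.0225) = 1.011 to 1/√(1 − 0.0625) = 1.033, about 1% to 3%.
- SD of the chance difference in C between two arms: √(2 × 0.25/42) = 0.109, about 11 percentage points.
- Typical shift in the arm difference: 0.109 × 0.3 = 0.03 SD to 0.109 × 0.5 = 0.05 SD, against a standard error of √(2/42) = 0.22 SD.

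**The case against.** The strongest objections concern consequence.

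**Baseline MBI absorbs much of the effect.** The MBI is measured before treatment (Table 4), in patients whose stroke was 3 to 12 months before enrolment. If the shared specification is read naturally, the MBI model adjusts for baseline MBI, although the text literally names baseline VAS. Much of the effect of a paretic dominant hand would then already be in the baseline score. This stands and limits the gain to what remains after baseline.

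**The MBI is only partly a hand measure.** It "covers domains such as feeding, dressing, toileting, continence, and mobility", and the last two domains depend less on the hand, so the effect on the total is diluted. This also stands.

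**The covariate does what its words say.** It adjusts for dominance itself, and no section states that dominant-limb involvement drives compensation. That is literally true. But the article justifies the term by functional compensation, and dominance without side is a poor measure of that.

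**Stronger readings.** A reader might infer that the MBI comparison is biased. It is not: allocation is randomised, and the ordinary confidence interval already reflects chance imbalance in an unadjusted factor. A reader might also infer that the covariate captures nothing at all. That is exact only if paretic sides are evenly split within each dominance group, which the article does not state; otherwise a small correlation remains.

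**Conclusion.** The point holds as a minor improvement. As coded, the covariate largely misses its stated purpose: it explains 0% to about 9% of the variance in whether the dominant hand is the paretic one, given 85-95% right-handers, 40-70% right paresis and independence, all of which are assumptions.

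The practical loss is about 1% to 3% in the standard error and a typical chance shift of 0.03 to 0.05 SD that goes unadjusted, if dominant-limb involvement moves baseline-adjusted MBI by an assumed 0.3 to 0.5 SD. This concerns a secondary outcome. No planned test is invalidated, and the primary VAS model, which has no dominance term, is untouched. The coding fact is certain; the size of its effect on the MBI is not known from the article.

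**What to change.** - In Descriptive statistics, replace the right/left category with a derived baseline variable, *dominant upper limb affected: yes/no* (yes when the pre-stroke dominant side equals the paretic side).
- Under Baseline, list paretic side as a recorded item. It is not named there now, but it must be known for every participant to confirm eligibility and place the coil.
- Use the variable in the MBI mixed model and in any other mixed model for which compensation is the stated reason, and name those outcomes. The ordinal outcomes analysed by GEE fall outside that sentence and need no change on this account.
- Under Secondary outcomes analysis, list the term for those models, because the shared specification has no dominance term, and say that the baseline value of the outcome itself is used.

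Cost: wording and one explicit baseline field. One parameter replaces one parameter, with no added assessments or participants. The change should be made before unblinding so that it stays pre-specified.
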